#### Study intervention

The communication skills training will be conducted with up to 10 physicians per group. Each cooperating site will consecutively run 2–3 training cycles. The training of each group will consist of two sessions, each lasting 90 min. There will be approximately two weeks between both sessions. The training will be carried out by two trainers: the leading investigator of the respective study site with expert knowledge in palliative care and a researcher with expert knowledge in communication and psychooncology. Contents and schedule are standardized through the manual. To ensure adherence, the trainers will fill out a training protocol after the training.

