#### Sample size and power

Sample size calculation indicates that a total sample size of 134 participating physicians (67 per group) is needed to detect medium group differences (Cohen’s *d* = 0.5) in a two tailed test with a power of 0.80 (80%) at a significance level of *p* < 0.05. A medium correlation (*r* = 0.3 [40]) between initial level and outcome measurement is assumed. Based on an estimated dropout-rate of 30%, recruitment of 174 physicians (87 per group) is necessary.

This amount of participating physicians will be recruited consecutively in groups of 10 and equally divided between the four study sites. For the recruitment, information material will be spread in local oncological networks, at conferences and events.

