### Data analyses

This study is a multivariate, two-armed RCT with repeated measurement points across time. Descriptive statistics will be used to characterize and describe groups (IG and CG). Using univariate analyses (t-test, analysis of variance) or comparable non-parametric tests (chi-square-tests, U-tests), differences between subgroups (e.g. age, medical specialization, level of working experience, work setting) will be explored.

In order to measure the success of the training, covariate-adjusted linear mixed models will be conducted for analyzing primary and secondary outcome variables. The considered covariates will be the initial level of outcome variables at T0. This method allows to also consider missing data. For non-repeated continuous and binary measurements, ordinary linear regression and logistic models will be used.

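### Only the intervention arm is trained in groups, and the stated 80% power makes no allowance for correlation within those groups

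*Protocol article*

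**What the plan says.** All of this is in the Methods of the protocol article.

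- **Randomization:** allocation is by individual physician, 1:1, in blocks of 20 within site.
- **Study intervention:** "The communication skills training will be conducted with up to 10 physicians per group", with 2–3 cycles per site. Two trainers lead each group, one of them the site's leading investigator.
- **Design** and **Evaluation of the training (RCT):** the control group is measured in parallel and trained only after data collection has finished.
- **Sample size and power:** a "total sample size of 134 participating physicians (67 per group) is needed to detect medium group differences" of d = 0.5, "in a two tailed test with a power of 0.80 (80"%), at the 5% level. A correlation of 0.3 "between initial level and outcome measurement is assumed". With 30% dropout the recruitment target is 174. No ICC, design effect or number of training groups enters.
- **Data analyses:** covariate-adjusted linear mixed models are planned. "The considered covariates will be the initial level of outcome variables at T0". The random effects are not described.

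**The concern.** Physicians trained together share peers, trainers, role plays and discussion, so their T1 communication scores may be more alike than those of physicians from different groups. At T1 such groups exist in one arm only, which makes this a partially nested design (an individually randomised group-treatment trial).

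Positive correlation within groups increases the variance of the intervention-arm mean. The degrees of freedom for that variance are also governed by about 8–12 groups rather than by 67 physicians.

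Two things are at stake. The power stated for the primary comparison is too high whatever model is fitted, because the calculation allowed nothing for clustering. In addition, if the fitted model omits training group, the standard error is too small and the test rejects too often.

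**Working it through.** **Inputs from the article.** d = 0.5; two-sided alpha 0.05; r = 0.3; 67 per arm evaluable; 174 recruited; 30% dropout; 2–3 cycles × 4 sites = 8–12 groups.

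**Assumed, because the article gives no figure.** ICC 0.02, 0.05 and 0.10, taken as the ICC of the baseline-adjusted outcome. Nine groups, since 87 / 10 = 8.7.

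**The plan's own figure.**
- An unadjusted t-test at d = 0.5 needs 64 per arm and has 81.9% power at 67.
- A Mann–Whitney test with efficiency 3/π = 0.955 gives 67 per arm after rounding up, which matches the article.
- Covariance adjustment at r = 0.3 (variance × 0.91) needs 59 per arm.

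The sponsor's formula is not stated. The article's figure is reproduced by an individual-level formula with no clustering term.

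**Power with clustering in the intervention arm only.** For n per arm, k groups and m = n/k:
- design effect DE = 1 + (m − 1) × ICC
- Var(IG mean) = 0.91 × DE / n; Var(CG mean) = 0.91 / n
- df = (V_IG + V_CG)² / [V_IG²/(k − 1) + V_CG²/(n − 1)]
- power from the noncentral t with noncentrality 0.5 / √(V_IG + V_CG)

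Example, n = 67, k = 9, ICC 0.05:
- m = 7.44 and DE = 1 + 6.44 × 0.05 = 1.322
- V_IG = 0.01796 and V_CG = 0.01358, so SE = 0.1776
- noncentrality = 2.815, df = 23.1, power = 77%

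| ICC | DE, 67/arm | df | Power | DE, 61/arm | df | Power |
|---|---|---|---|---|---|---|
| Independent physicians, full df | – | 132 | 85% | – | 120 | 82% |
| 0, same df method | 1.000 | 28.5 | 83% | 1.000 | 28.2 | 80% |
| 0.02 | 1.129 | 26.0 | 81% | 1.116 | 26.0 | 77% |
| 0.05 | 1.322 | 23.1 | 77% | 1.289 | 23.4 | 74% |
| 0.10 | 1.644 | 19.8 | 71% | 1.578 | 20.3 | 68% |

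The 61 per arm is what remains of 174 after 30% loss: 174 × 0.70 / 2 = 60.9.

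**Number of groups, 67 per arm.** At ICC 0.02, 0.05 and 0.10, eight groups give 80.0%, 75.5% and 68.5%; twelve groups give 82.3%, 79.6% and 75.3%.

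**Type I error if training group is omitted.** A test that ignores groups uses a variance too small by the factor (DE + 1)/2, so its size is about 2 × [1 − Φ(1.96 / √((DE + 1)/2))].
- 67 per arm: 5.7%, 6.9% and 8.8% at the three ICCs
- 61 per arm: 5.7%, 6.7% and 8.4%

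Simulation with nine groups agrees to within about 0.2 percentage points.

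**The case against.** **The analysis may already handle this.** The planned method is a linear mixed model, and the sentence on covariates concerns fixed effects. A training-group random effect would not be listed there, and a condensed article can leave random effects to a fuller document. This stands. A reader might infer that the planned analysis treats physicians as independent and that its test is anti-conservative. The article does not say so, and the type I figures apply only if training group is left out. The objection does not rescue the sample size, which is a stated calculation. Adding the term protects the type I error, but the power loss remains.

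**80% power may survive.** A reader might also infer that 80% is out of reach. It is not: at 67 per arm with nine groups it holds up to an ICC of about 0.02, and with twelve groups to just under 0.05. The unused gain from r = 0.3 absorbs a small ICC.

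**Some of the drop has other causes.** At 67 per arm about 2 points (85% to 83%) come from the few-group degrees of freedom before any correlation enters. The lower figures at 61 per arm also reflect how 174 was obtained (134 × 1.3 = 174.2), which is a separate matter. The like-for-like effect of the ICC is the fall from 83% at 67 per arm.

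**The ICC may be small.** The training is two manual-based 90-minute sessions, trainers attend a common workshop, and outcomes come from individually arranged consultations 6–10 weeks later, rated blind. These facts make a modest ICC credible, but they do not show that it is zero.

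**Conclusion.** The point holds for the sample size and conditionally for the analysis. The stated 80% power is optimistic because clustering confined to the intervention arm was not allowed for. With nine groups and r = 0.3 adjustment, power at 67 per arm is about 81%, 77% and 71% at assumed ICCs of 0.02, 0.05 and 0.10. If the stated 30% dropout leaves 61 per arm, it is 77%, 74% and 68%. The true loss cannot be fixed from the article, since it rests on an ICC that is not given.

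Inflated type I error, up to about 8.8% at ICC 0.10, is a risk only if the final model has no training-group term. This should be fixed, but it does not invalidate the design.

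**What to change.** 1. Record a training-group ID for every intervention-arm physician.
2. In Data analyses, specify a partially nested mixed model for primary and secondary outcomes: a training-group random effect in the intervention arm only, each control physician treated as a singleton, and Satterthwaite or Kenward–Roger degrees of freedom.
3. In Sample size and power, replace the single 80% with power over ICC 0–0.10, stating the number of groups assumed. N need not change.

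The cost is one recorded variable and some wording. The downside is slightly wider confidence intervals and, with only 8–12 groups, a group variance that may be estimated at zero.

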#### Evaluation

The evaluation of the training will be carried out by comparing the pre (T0)-post (T1) differences of consultation performance of the IG and the CG. Therefore, the participants of IG and CG will conduct a videotaped medical consultation on palliative care related topics with a SP at T0 and T1. The consultations will be arranged individually between the physician and the SP and will take place in the familiar working environment of the physician. No further study assistant will be present, so that the setting is kept as naturalistic as possible.

### Outcomes and measurement

Table 1 displays an overview of collected data, instruments, measurement points and sources of data. Measurements consist of external and self-assessed items. The following instruments will be used regarding our primary and secondary study outcomes.

**Table 1 Tab1:** Overview of study measures

Measures	Instrument	Baseline/ Pre-Training (T0)	Post-Training (T1)	Source of data
Communication skills and consulting competencies addressing palliative care related topics	German version of the COM-ON-Checklist	**●**	**●**	External assessment by researchers
Consideration of palliative care principles	Self-developed questionnaire based on EAPC-competencies	**●**	**●**	External assessment by researchers
Quality of physician-patient-interaction	German version of the Questionnaire on the Quality of Physician-Patient-Interaction (QQPPI)	**●**	**●**	External assessment by simulated patients
Sociodemographic data	Self-developed items	**●**		Physician self-report
Confidence in dealing with palliative care related topics	Self-developed items	**●**	**●**	Physician self-report
Self-efficacy regarding conversations about palliative care	German version of Self-Efficacy in Palliative Care Scale (SEPC)	**●**	**●**	Physician self-report
Attitude towards caring for terminally ill patients	German version of Thanatophobia-Scale	**●**	**●**	Physician self-report
Knowledge about palliative care services	Self-developed items	**●**	**●**	Physician self-report
Acceptance of and satisfaction with training	Self-developed items		**●**	Physician self-report

#### Primary outcome

##### Communication skills and consulting competencies addressing palliative care related topics

In order to assess the consultation performance of the physicians, we will develop different case vignettes, which will be varied systematically between the measurement points. While the severity of the disease will be comparable, the type of symptoms and the patient’s needs will differ from case to case.

Communication skills and consulting competencies addressing palliative care related topics will be assessed by the research team using the German version of the COM-ON-checklist (COM-ON = *Communication in Oncology*) [41], which is a valid instrument for the external assessment of communication behavior of oncologists consisting of 5 scales and 31 Items. Researchers will rate the videotaped physician-patient-consultations on a 5-point Likert scale by the following scales: *general communication skills*, *specific skills: transition to palliative care*, *involvement of relatives* and *overall evaluation items*. The fifth scale named *disclosing information about clinical trials* will be excluded, because in this context no such information has to be given, so that only 21 items are used. The instrument has proved to be valid and reliable [41].

To ensure independent and blinded rating of the consultation, we will rotate the videotapes between the four research sites. Thus, the rater will not have any information on group membership (IG or CG) of the respective participant.

#### Secondary outcomes: external assessments

##### Consideration of palliative care principles

We will develop a study-specific questionnaire consisting of items based on the EAPC-competencies [36] to assess the application of palliative care principles. With this questionnaire the consultation competence regarding palliative care will be externally assessed by the researchers.

##### Quality of physician-patient-interaction

A further external evaluation of the consultation is carried out by the SPs with the German version of the Questionnaire on the Quality of Physician-Patient-Interaction (QQPPI) [42]. A 5-point Likert-scale from (1) strongly disagree to (5) strongly agree is used. The total score is determined by the mean value of all items. The instrument has proved to be valid and reliable [42].

#### Secondary outcomes: self-report

##### Confidence in dealing with palliative care related topics

The physician’s perceived confidence will be assessed by study-specific, self-developed items.

##### Self-efficacy regarding conversations about palliative care

A German version of the Self-Efficacy in Palliative Care Scale (SEPC) [43] will be used to assess self-efficacy. It consists of 23 items, which assess the constructs of self-efficacy and outcome expectancies in palliative care. Each subscale represents different target behaviors and skills, upon which the study participant rates his or her confidence in his or her ability to perform the respective behavior or skill on a 100 mm visual analogue scale ranging from (0) very anxious to (10) very confident. The SEPC is a valid and reliable questionnaire [43].

##### Attitude towards caring for terminally ill patients

To measure this construct, we will make use of the Thanatophobia-Scale [44], a short questionnaire that addresses feelings associated with fear of death among healthcare professionals. The 7 items measure discomfort in dealing with dying patients on a seven-point Likert scale ranging from (1) strongly disagree to (7) strongly agree. A total score is calculated by summing all items. The Thanatophobia-Scale has proved to be valid and reliable [43, 44].

##### Knowledge about palliative care services

Basic knowledge concerning palliative care services will be assessed by study-specific, self-developed items.

##### Acceptance of and satisfaction with the training

The participants’ perception concerning the quality of the training will be assessed after the training by study-specific, self-developed items, supplemented by few open questions.

### Data analyses

This study is a multivariate, two-armed RCT with repeated measurement points across time. Descriptive statistics will be used to characterize and describe groups (IG and CG). Using univariate analyses (t-test, analysis of variance) or comparable non-parametric tests (chi-square-tests, U-tests), differences between subgroups (e.g. age, medical specialization, level of working experience, work setting) will be explored.

In order to measure the success of the training, covariate-adjusted linear mixed models will be conducted for analyzing primary and secondary outcome variables. The considered covariates will be the initial level of outcome variables at T0. This method allows to also consider missing data. For non-repeated continuous and binary measurements, ordinary linear regression and logistic models will be used.

### Study status

The project duration is 36 months. The study was initiated in March 2019. The first 12 months are dedicated to the first study phase including extensive preparatory work, focus groups as well as development and manualization of the training. Recruitment of participants will start in April 2020. Data collection of both measurement points is planned to be completed by October 2021.

### Ethics and consent

We will provide written information material to study participants and SP, who both must provide informed consent before data collection. The study protocol and other requested documents were reviewed and approved by the medical ethics committee of the Medical Chamber of Hamburg (date: 19 November 2018, number: PV5910).

### Data confidentiality

To ensure confidentiality, data will be stored pseudonymized on a secure database in accordance with the General Data Protection Regulations [45]. Information and measurements of the study participants collected during the study will be stored separately from the personal information. Extensive considerations on data protection with the data protection officer of the University Medical Center Hamburg-Eppendorf were carried out.

## Discussion

The aim of this study project is to evaluate a communication skills training that addresses physicians’ ability to communicate adequately and early about palliative care related topics. To the best of our knowledge, this is the first randomized controlled trial for such training. Few communication skills trainings on palliative care related topics do exist, but those solely focus on communicating single, specific facets of palliative care [30, 33, 34].

earlyEarly integration of palliative care into the care of advanced cancer patients is recommended by various guidelines [2, 15, 18]. However, different barriers on part of the physicians impede this. A major barrier and reason for the avoidance of referring to palliative care is communicating the associated topics to patients, which at the same time is regarded a fundamental component of integration [20]. Once completed, the project will provide an evidence-based approach to reduce those communication barriers. Accordingly, future use of the training program will promote an earlier referral to palliative care in the care of advanced cancer patients. This is associated with several advantages not only for patients and their caregivers, but also for the health care system, as it reduces costs [15] by providing less aggressive care at the very end of life [46]. Since the training is designed for physicians of different specialization treating cancer patients, the intervention addresses a broad clientele. The assessment of several outcome variables with external and self-assessment instruments in our study will allow for a comprehensive, multiperspective insight into the effectiveness of the training. This will enable conclusions on future interventions, further research and the feasibility of similar trials. A limitation of the study represents a potential selection bias. Due to the voluntary participation, it might be that those physicians take part, who already have a higher interest or competence in physician-patient communication. However, ethical guidelines prevent a subsequent non-responder analysis, so that this circumstance cannot be analyzed.

The study results will be disseminated through publication in peer-reviewed scientific journals and presentations on scientific meetings and conferences.

In conclusion, this randomized controlled trial will provide a feasible intervention designed for a broad range of recipients to promote earlier communication about palliative care and end-of-life topics.

## Data Availability

Not applicable.

## Abbreviations

CG: Control group
COM-ON: Communication in Oncology
CReDECI2: Criteria for Reporting the Development and Evaluation of Complex Intervention in healthcare
EAPC: European Association for Palliative Care
IG: Intervention group
KSA: Knowledge, Skills, Attitude
QQPPI: Questionnaire on the Quality of Physician-Patient-Interaction
RCT: Randomized controlled trial
SEPC: Self-Efficacy in Palliative Care Scale
SP: Simulated patients
